### Eligibility criteria

Inclusion criteria for participation in the study are: 1) age 65 years or older, 2) undergoing a lumbar spine fusion surgery, 3) expected duration of surgery < 3 h, 4) under the care of a participating surgeon, and 5) expected ability to understand and comply with study procedures. Exclusion criteria are: 1) contraindications to spinal anesthesia (e.g. severe aortic stenosis, anti-coagulant or anti-platelet therapy), 2) BMI > 40, 3) prior L2–5 full lumbar fusion, 4) communication issues precluding baseline assessments, 5) baseline dementia or MMSE < 24, 6) psychiatric disease that would preclude cooperation with sedation with spinal anesthesia, and 7) attending surgeon or anesthesiologist preference for either spinal or general anesthesia for any reason due to clinical considerations.

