### Sample size

Assuming a delirium incidence of 35% in the control and a 50% reduction in the intervention group [2, 20], 206 patients would be needed to show a difference in incidence of delirium at a 0.05 significance level with a power of 0.8. With an estimated 6% withdrawal, the target enrollment is 218 patients. The expected sample size of 206 patients will also be sufficient for the secondary outcome of MMSE change at 3-months after surgery: the minimum detectable change in MMSE with 206 patients is ±0.235 at a 0.05 significance level with a power of 0.8.

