It is expected that < 10% of patients randomized to receive spinal anesthesia will actually receive general anesthesia due to failure to obtain spinal anesthesia. If patients receive both a spinal and general anesthetic, they will be categorized into an appropriate group for the on-treatment approach based on the biologic hypothesis for each analysis. For the purposes of the primary analysis on-treatment approach, they will be considered to have received deep anesthesia.

In a sensitivity analysis, we will consider accounting for crossover based on an inverse-probability of treatment weighting approach. This approach will provide an estimate of the difference in the incidence of delirium comparing the intervention and control groups, had all patients received their randomized treatment. Other sensitivity analyses will include: a) an as-treated analysis, b) re-estimation of both of the above treatment effects after adjustment for select baseline covariates, including age, education, and cognitive score [36], with consideration of gender, race, and other variables associated with incidence of delirium in bivariate analyses, and c) pre-specified subgroup analyses based on stratifying patients by age (< 75 vs. > 75 years old), baseline Charlson Comorbidity Index (0 vs. > 0), and baseline cognition (MMSE < 27 vs ≥27, or lowest quartile vs upper quartiles, dependent upon the baseline distribution). Confidence intervals and *p*-values will be generated via a bootstrap procedure using 5000 bootstrap samples.

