The most important secondary outcome is change in MMSE (or Telephone Interview for Cognitive Status [TICS]) [37]. Change in MMSE/TICS will be analyzed using linear regression analysis, first unadjusted, and then with adjustment for age and education, with consideration of gender, race, and other variables associated with change in MMSE/TICS in bivariate analyses. If TICS is > 50% of responses, we will use item response theory to compare similar or exact items on the TICS and MMSE. The treatment effect will be defined as the difference in the change in MMSE/TICS at three months comparing the intervention and control groups. Other pre-specified secondary outcomes that will be compared between groups by domain are listed in Table 2 and include: (1) delirium severity and number of days of delirium, (2) change in each individual cognitive test score), (3) change in function, disability and quality of life (Instrumental Activities of Daily Living score [38] [any decline], Oswestry Disability Index score [39], Short Form (SF)-12 Physical Component Summary, SF-12 Mental Component Summary [40], (4) hospital utilization (readmissions, emergency department visits, duration of hospitalization, and (5) pain (pain in the postoperative anesthesia care unit, hospital pain, and post-discharge pain. The main post-discharge outcomes will be measured at 3-months. However, we will also collect and report data at 12-months after surgery. For continuous and binary secondary outcomes, similar methods as described above will be applied. We anticipate that delirium severity and number of days of delirium will be highly skewed and will be analyzed as ordinal or dichotomous variables.

Other pre-specified analyses include examining (1) the association of delirium and hospital utilization and other post-discharge outcomes (2) the association of BIS values and burst suppression with postoperative delirium and cognitive change, and (3) risk factors for decline in cognition, function, or health-related quality of life after spine surgery. In all analyses, a value of *p* < 0.05 will be considered significant. Due to the number of outcomes that will be examined (beyond incident delirium and change in MMSE), the analyses of secondary outcomes will be considered preliminary and hypothesis-generating.

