### Strengths and limitations

The SHARP study has many important strengths. The trial is pragmatic and is conducted in a real-world clinical setting using standardized anesthetic approaches. The outcome of delirium is highly significant, and other outcomes are also important to both patients and clinicians. The intervention is not expensive and is able to be implemented by anesthesia providers using standard approaches. The investigative team is experienced in clinical studies in the perioperative setting using delirium as a primary outcome. The following limitations should be considered. The results of this single clinical trial in the spine surgery population would likely not be considered definitive, and subsequent studies would be needed to replicate any findings suggesting benefit to the intervention group (regardless of *p*-value). Some patients may not be appropriate for spinal anesthesia, and some anesthesia providers prefer general anesthesia with endotracheal intubation to secure the airway of patients in a prone patient. Thus, the results of this study may not be generalizable. The trial may be underpowered since a 50% reduction of delirium is assumed for the sample size estimation, and the estimate of 35% incidence of delirium may be too high in the control arm (with several large studies in non-cardiac surgery patients estimating an incidence of delirium in the 22–26% range [9, 16]. Nevertheless, a sample size of > 200 will provide important information. The intervention is a bundle of spinal anesthesia with targeted sedation with propofol, and thus if the intervention is effective, then further studies will be needed to understand precise mechanisms. Nevertheless, the trial design allows the comparison of “deep” general anesthesia with lighter levels of anesthesia than would be ethical to administer with general anesthesia. The trial design also reflects real-world clinical practice in anesthetic approaches. Outcome assessors at 3- and 12-months are not masked due to study logistical constraints. However, these assessments are highly standardized and the potential for bias is small. We also anticipate missing follow-up assessments at both 3- and 12-months due to patient retention in this cohort of older adults. As the MMSE cannot be administered over the telephone, we need to use another instrument to assess cognition for telephone follow-up. The TICS is the most widely used telephone instrument for assessment of global cognitive function, correlates well with the MMSE, and TICS scores and cutpoints have been directly linked to MMSE scores [41]. Finally, the MMSE has important limitations to consider, including practice and ceiling effects that may bias the results [42].

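### Baseline MMSE is not a fixed covariate in the analysis of change in MMSE/TICS and can enter only by data-driven selection; the comparison stays valid, but precision is given up, by a small to material amount

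*Protocol article*

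**What the plan says.** All places are in the Protocol article.

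- **Model for the main secondary outcome** (Data and statistical analysis): "Change in MMSE/TICS will be analyzed using linear regression analysis, first unadjusted, and then with adjustment for age and education". The sentence goes on: "with consideration of gender, race, and other variables associated with change in MMSE/TICS in bivariate analyses".
- **Treatment effect** (same section): "The treatment effect will be defined as the difference in the change in MMSE/TICS at three months comparing the intervention and control groups".
- **Other outcomes** (same section): "For continuous and binary secondary outcomes, similar methods as described above will be applied".
- **Delirium sensitivity analysis** (same section): re-estimation after "adjustment for select baseline covariates, including age, education, and cognitive score".
- **Entry restriction** (Eligibility criteria): patients are excluded for "baseline dementia or MMSE < 24".
- **Known limits of the score** (Strengths and limitations): "the MMSE has important limitations to consider, including practice and ceiling effects that may bias the results".
- **Precision claimed** (Sample size): "the minimum detectable change in MMSE with 206 patients is ±0.235 at a 0.05 significance level with a power of 0.8". No SD and no baseline-to-follow-up correlation accompany this figure.

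**The concern.** Change from baseline is usually negatively related to the baseline value. Patients who score high at entry have little room to rise, and patients just above the entry limit tend to drift up. Entry is cut at 24 and the protocol concedes a ceiling, so some such dependence is to be expected here.

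Where change depends on baseline, a model without baseline leaves explainable variation in the residual. It also lets part of any chance difference between arms at baseline into the estimated effect. The protocol treats baseline cognition as worth naming when it adjusts delirium, but not when the outcome is cognition itself.

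At stake is the precision of an outcome that has its own hypothesis and its own detectable difference. The plan's multiplicity caveat also sets it apart from the remaining secondary outcomes. A second issue is that whether baseline is adjusted for would be settled only after outcome data have been examined.

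**Working it through.** **1. The plan's own figure.** The detectable difference of ±0.235 cannot be reproduced, because no SD is given; it can only be back-solved (two-sided 0.05 assumed).
- Two arms of 103: (1.960 + 0.842) × √(2/103) = 0.390 SD, so SD of change = 0.235/0.390 = 0.60.
- One sample of 206: 2.802/√206 = 0.195 SD, so SD of change = 0.235/0.195 = 1.20.

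Neither reading implies baseline adjustment.

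**2. Precision.** Let s1 and s2 be the baseline and follow-up SDs and rho their correlation (all assumed).
- Change score: variance = s1² + s2² − 2·rho·s1·s2.
- Baseline-adjusted: variance = s2²(1 − rho²).
- The difference is (s1 − rho·s2)², which is never negative, so in large samples adjustment cannot lose.

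With s1 = s2 the ratio, adjusted to change score, is (1 + rho)/2. With s1/s2 = 0.8 it is (1 − rho²)/(1.64 − 1.6·rho).

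| rho | ratio, s1/s2 = 1 | ratio, s1/s2 = 0.8 |
|---|---|---|
| 0.3 | 0.65 | 0.91/1.16 = 0.78 |
| 0.5 | 0.75 | 0.75/0.84 = 0.89 |
| 0.7 | 0.85 | 0.51/0.52 = 0.98 |

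The detectable difference scales with the square root. If 0.235 is an unadjusted two-arm figure, at rho 0.5 it becomes 0.235 × √0.75 = 0.204 with equal SDs, or 0.235 × √0.89 = 0.222 with ratio 0.8. At rho 0.7 and ratio 0.8 it is 0.233, almost no change.

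A simulation of an integer score capped at 30 (taken as the scale maximum; the protocol does not state it), with baseline restricted to 24 or above, gave variance ratios of 0.64 to 0.91. Slopes of change on baseline were −0.22 to −0.73. The simulated SD ratios were about 0.91 to 0.99, so 0.8 is a harsher case than any simulated.

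**3. Chance imbalance.** If the arms differ by d at baseline and follow-up regresses on baseline with slope b, the change-score estimate shifts by (b − 1)·d.
- Assumed baseline SD 1.3 to 1.8: one standard error of d is SD × √(2/103) = 0.18 to 0.25 points.
- b = 0.5: shift of 0.09 to 0.13 points.
- b = 0.875 (rho 0.7, SD ratio 0.8, since b = rho·s2/s1): 0.125 × 0.18 to 0.25 = 0.02 to 0.03 points.

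The upper case is 39% to 53% of 0.235. That comparison flatters the concern, because such baseline SDs do not sit easily with a change SD of 0.60. With SD 1.5, equal SDs and rho 0.5, the SD of change is also 1.5. The two-arm detectable difference is then 1.5 × 0.390 = 0.586, and the shift of 0.105 is 18% of it.

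**4. Would the bivariate screen find baseline MMSE?** With equal SDs the correlation of change with baseline is −√((1 − rho)/2), or −0.63 at rho 0.2 and −0.32 at rho 0.8. With 206 patients it reaches p < 0.05 with probability above 99%. Baseline would very probably be flagged, but the text promises only consideration.

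**The case against.** The strongest reply is that the plan does not shut baseline MMSE out. The sentence on covariates allows for other variables associated with change, and step 4 shows that baseline would almost surely qualify. This stands against any claim that the plan excludes baseline adjustment. It does not answer the narrower point: the choice is made after seeing outcome data, no rule commits the analyst to it, and the unadjusted model is unaffected.

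Readers might also infer more than the protocol supports:
- **That the change-score result is biased.** It is not. Allocation is randomised 1:1, and a difference in change is a valid comparison on average.
- **That a baseline difference passes whole into the effect.** A change score already subtracts baseline; only the fraction (b − 1) remains.
- **That the trial wastes a fixed share of its patients.** At rho 0.5 with equal SDs the change score needs 1/0.75 = 1.33 times as many patients. With an SD ratio of 0.8 this is 1/0.89, or about 1.12 times. Equal SDs cannot be taken for granted when only baseline is truncated at 24. Age, education and other selected covariates may also capture part of the gain already.
- **That baseline adjustment answers the ceiling problem.** A linear model with baseline does not remove a ceiling, and the protocol already discloses it.
- **That the article is at fault for not ranking its two models.** That can be left to the analysis plan, which is not shown.

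**Conclusion.** The point holds as a modest one of efficiency and pre-specification on a secondary outcome. The adjusted model for change in MMSE/TICS fixes age and education but not baseline MMSE, which the same section thought worth naming for delirium.

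Across the assumptions worked here, baseline adjustment multiplies the variance of the treatment effect by between 0.65 (rho 0.3, equal SDs) and 0.98 (rho 0.7, SD ratio 0.8). The gain therefore runs from material to negligible. The protocol gives neither the SDs nor the correlation needed to narrow this. These ratios compare with the unadjusted change score, so the gain over the age-and-education model may be smaller. Validity under randomisation is not in question.

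**What to change.** In Data and statistical analysis, name baseline MMSE as a fixed covariate with age and education in the adjusted model for change in MMSE/TICS, and take it out of the bivariate screen. The unadjusted change can still be reported. On one metric the treatment coefficient is the same whether the outcome is the change or the 3-month score, because subtracting baseline alters only the baseline coefficient. The stated definition of the treatment effect is therefore kept. Add a sentence on how baseline MMSE is used when the follow-up score is a TICS.

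Use the matching baseline value in the same way for the other continuous change outcomes: ODI, SF-12 PCS and MCS, verbal fluency, Trail Making and digit span. All are in the baseline schedule of Table 1. Post-discharge pain is not included, because Table 2 defines it as an average score and not as a change.

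The cost is a few sentences of analysis wording. No new data are needed, since baseline MMSE is already required for eligibility. The ceiling effect stays a stated limitation.

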### Baseline and follow-up assessments

Patients undergo assessments prior to surgery and at 3- and 12-months postoperatively as described in Table 1. After surgery, research staff administer assessments in person at the 3-month clinical follow-up appointment, or by telephone in the case that follow-up assessments cannot be coordinated in person. The 12-month assessment is administered by telephone. Retention will be encouraged during each of these visits.

**Table 1 Tab1:** Baseline and Follow-up Standardized Assessments

Neuropsychological Assessments	
Mini-Mental Status Examination ^a^	
Verbal Fluency Trials from the Calibrated Ideational Fluency Assessment	
Trail Making Test ^b^	
Digit Span Forwards/Backwards	
Function, Disability, and Health-Related Quality of Life Assessments	
Instrumental Activities of Daily Living	
Oswestry Disability Index	
12-Item Short Form Health Survey	
Pain scores	

^a^In the case of a telephone interview, the Telephone Interview for Cognitive Status is used

^b^The Trail Making Test is not administered in the case of telephone interview

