### Other secondary outcomes

Additional domains that are important for postoperative recovery will be examined as secondary outcomes. These domains include: duration and severity of delirium, other tests of cognition, functional status, disability, health-related quality of life, health care utilization, and pain. The specific tests and outcomes for each of these domains are listed and defined in Table 2.

**Table 2 Tab2:** Primary and Secondary Outcomes

Domain	Outcome	Definition
Delirium	Incident delirium *(Primary Outcome)*	Any CAM (+) assessment
	Delirium severity	Maximum DRS-R-98 score
	Number of days of delirium	Number of CAM (+) days
Cognition	Change in MMSE/TICS	Change in score. Item response theory will be used to compare similar or exact items if TICS> 50% of responses.
	Change in other individual test scores	Verbal Fluency (all trials combined, sum of scores), TMT-A (time), TMB-B - TMT-A (time), DSF (longest span correct), DSB (longest span correct)
Function	Any decline in IADL score	Any decline in IADL score from baseline to 3- and 12-month follow-up
Disability	Change in ODI score	Change in ODI score (%) from baseline to 3- and 12-month follow-up
Health-Related Quality of Life	Change in SF-12 PCS	Change in PCS score from baseline to 3- and 12-month follow-up
	Change in SF-12 MCS	Change in MCS score from baseline to 3- and 12-month follow-up
Health Care Utilization	Readmissions	% Readmissions
	Emergency department visits	% Emergency department visits
	Duration of hospitalization	Number of days in hospital after surgery
Pain	PACU pain	Last pain score in PACU.
		Total morphine equivalents
		Time to first opoid
	Hospital pain	Last pre-discharge pain score.
		Total morphine equivalents, pro-rated for 72 h in hospital
	Post-discharge pain	Average pain score at 3- and 12-month follow-up

Abbreviations: *CAM* Confusion Assessment Method, *DRS-R-98* Delirium Rating Scale-Revised 1998, *MMSE* Mini-Mental State Examination, *TMT* Trail Making Test, *DSF* Digit Span Forward, *DSB* Digit Span Backwards, *IADL* Instrumental Activities of Daily Living, *ODI* Oswestry Disability Index, *SF-12* 12-Item Short Form Health Survey, *PCS* physical component summary, *MCS* mental component summary, *PACU* postoperative anesthesia care unit

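### The 3-month MMSE/TICS change has no stated conversion when TICS is 50% of responses or less, although every telephoned patient changes instrument

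*Protocol article*

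**What the plan says.** All references are to the protocol article.

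- **Instrument by mode.** Baseline and follow-up assessments, Table 1 footnote a: "In the case of a telephone interview, the Telephone Interview for Cognitive Status is used". The same section makes the 3-month assessment in person, with telephone as the fallback, and the 12-month assessment by telephone for everyone.
- **Baseline instrument.** Eligibility criteria exclude patients with an MMSE below 24, and one planned subgroup splits on baseline MMSE. The baseline score is therefore an MMSE.
- **Outcome definition.** Table 2 under Other secondary outcomes names the outcome "Change in MMSE/TICS" and defines it as follows: "Change in score. Item response theory will be used to compare similar or exact items if TICS> 50% of responses".
- **Analysis.** Data and statistical analysis: "Change in MMSE/TICS will be analyzed using linear regression analysis, first unadjusted, and then with adjustment for age and education". The trigger is repeated there: when TICS exceeds 50% "of responses, we will use item response theory to compare similar or exact items on the TICS and MMSE". The estimand is a single pooled contrast: "The treatment effect will be defined as the difference in the change in MMSE/TICS at three months comparing the intervention and control groups".
- **Existing link.** Strengths and limitations, in defending the choice of telephone instrument, notes that "TICS scores and cutpoints have been directly linked to MMSE scores".

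**The concern.** A patient telephoned at 3 months has an MMSE before surgery and a TICS afterwards. Whether those two scores can be subtracted is a question about that patient. It does not depend on how many other patients were telephoned. If harmonisation is needed when 51% of responses are TICS, it is needed for each telephoned patient when 49% are. Yet the plan states a method only above the threshold.

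Two further features make the rule fragile. The count that triggers it arises after randomization, so the metric of the outcome is unknown until follow-up is complete. And the set of responses to be counted (3-month only, both follow-up visits, or all visits) is not defined.

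At stake is the interpretability of the outcome that the plan calls its most important secondary one. Data and statistical analysis exempts it from the hypothesis-generating label given to the remaining secondary outcomes, and Sample size gives it its own detectable-change statement.

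**Working it through.** **1. The plan's own figure.** Sample size states a minimum detectable MMSE change of ±0.235 with 206 patients, 0.05 significance and power 0.8, but gives no SD, so the figure cannot be reproduced. Read as a two-sided, between-arm difference with 103 per arm:

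- detectable difference = SD × (1.96 + 0.8416) × √(2/103) = 0.390 × SD
- implied SD = 0.235 / 0.390 ≈ 0.602

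The figure does not decide whether the 50% rule is sound. It matters only for which comparisons are legitimate later.

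**2. What the rule yields for each kind of 3-month patient.**

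| 3-month mode | Baseline | Follow-up | TICS share ≤ 50% | TICS share > 50% |
|---|---|---|---|---|
| In person | MMSE | MMSE | change in score, same instrument | item response theory on similar or identical items |
| Telephone | MMSE | TICS | change in score, no conversion stated | item response theory on similar or identical items |

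The telephone row at a share of 50% or less is the gap.

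**3. How the undefined count matters.** Assume equal numbers at each visit, TICS for all at 12 months, MMSE for all at baseline, and a 3-month telephone share p = 0.3:

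- 3-month visit alone: 30%, trigger not met
- both follow-up visits: (0.3 + 1)/2 = 65%, trigger met
- all three visits: (0 + 0.3 + 1)/3 ≈ 43%, trigger not met

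The same data give different methods depending on a definition the text does not supply.

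**4. Consequence if scores are left unconverted.** Let TICS totals sit d points from MMSE totals, let p be the telephone share, and assume mode is unrelated to true change. Then:

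- added variance within an arm = p(1-p)d²
- bias in the treatment effect = d × (difference in telephone share between arms)

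Neither d nor p is in the documents, and no SD of change is given. With SD = 2 (variance 4) and p = 0.3, all assumed:

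| d (assumed) | Added variance | Total variance | Ratio to 4 | Detectable difference, 0.390 × SD |
|---|---|---|---|---|
| 0 | 0 | 4.00 | 1.00 | 0.390 × 2.00 = 0.78 |
| 2 | 0.3 × 0.7 × 4 = 0.84 | 4.84 | 1.21 | 0.390 × 2.20 = 0.86 |
| 5 | 0.3 × 0.7 × 25 = 5.25 | 9.25 | 2.31 | 0.390 × 3.04 = 1.19 |

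With equal shares the bias is zero for any d. A hypothetical 10-percentage-point imbalance would give 0.1 × d, that is 0.2 points at d = 2 and 0.5 points at d = 5.

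**The case against.** The strongest reply is that the plan never says raw totals will be subtracted. The abstract allows a telephone equivalent of the MMSE, and Strengths and limitations cites an existing link between the scales. Read together, these could mean linked scores by default and item-level modelling once TICS dominates, with the conversion left to a fuller document. Part of this stands: unconverted subtraction is the plain reading, not an explicit instruction. But the link is cited to justify choosing TICS, nothing commits the analysis to it, and the only harmonisation rule stated is the conditional one.

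A second reply is that a threshold may have a practical reason. Item-level calibration needs enough TICS records, and a 10% share of 206 patients gives only about 20. This stands too: the article gives no reason for 50%, which does not show that none exists, and item-level modelling may not work at low shares. It argues for a different conversion at low shares, not for having none.

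Third, the trigger depends on mode of assessment and not on outcome values, and analysts are masked, so it offers little scope for steering the result. Agreed.

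A reader might also infer more than the documents support:

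- **That the treatment effect will be biased.** A constant offset cancels when telephone shares are equal, and nothing in the article suggests they will differ. Equal shares are not guaranteed, since mode is settled after randomization and neither patients nor 3-month assessors are masked, but an imbalance remains hypothetical.
- **That the bias would rival the stated ±0.235.** This mixes two SDs. The ±0.235 implies an SD near 0.60, whereas the illustration uses 2. At an SD of 2 the detectable difference is about 0.78, and a bias of 0.2 to 0.5 lies below it.
- **That the 12-month analysis has the same gap.** All 12-month assessments are by telephone, so the trigger is already exceeded if responses are counted by visit.

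**Conclusion.** The point holds as a badly set rule, of moderate severity. For the 3-month main secondary outcome, the plan states how to reconcile TICS with MMSE only above a 50% share. At or below that share it pools the changes in one regression with no stated conversion, although the instrument mismatch exists for every telephoned patient. The trigger depends on a post-randomization count of an undefined set of responses.

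The size cannot be fixed from the documents. Under the assumed SD of 2 and telephone share of 0.3, the variance of change rises 1.2-fold for a 2-point offset and 2.3-fold for a 5-point offset. The certain direction of harm is loss of precision if an offset exists and scores are not converted. Bias needs unequal telephone shares as well. The primary outcome, any positive in-hospital CAM, is untouched.

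**What to change.** For the 3-month main secondary outcome, replace the 50% trigger with one prespecified rule, fixed before analysis:

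- Place every TICS score on the MMSE metric whatever the telephone share, and compute change on that metric. Use the TICS-MMSE link cited in Strengths and limitations by default, and item-level item response theory where there are enough TICS records to support it, with that condition stated in advance.
- Report the telephone share at 3 months by arm.
- Add a sensitivity analysis restricted to patients assessed in person with the MMSE.

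If any share-based condition is kept, say which visit's responses are counted.

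The cost is revised analysis wording and a score conversion, with no new data. The downside is some linking error in the converted scores. The suitability of the cited link for this cohort could not be checked from the article and should be confirmed when the rule is written.
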